## 73 **1. Trial Information**

### 74 **1.1 Title**

75 Comparison of Peri-procedural Complications of Intracardiac Echocardiography and  
 76 Transesophageal Echocardiography in Patients With Atrial Fibrillation (ICE vs TEE  
 77 Study): A Multicenter Randomized Controlled Trial

78

### 79 **1.2 Trial Registration**

- 80 • Primary Registry: ClinicalTrials.gov
- 81 • Trial Identifying Number: NCT05466266
- 82 • Date of Registration: 2021-12-15
- 83 • Scientific Title: Comparison of Peri-procedural Complications of Intracardiac
- 84 Echocardiography and Transesophageal Echocardiography in Patients With
- 85 Atrial Fibrillation (ICE vs TEE Study)
- 86 • Public Title: ICE vs TEE Study
- 87 • Countries of Recruitment: China
- 88 • Health Conditions Studied: Atrial Fibrillation
- 89 • Intervention(s):

- 90 1. ICE group: Intracardiac echocardiography for LAA thrombus screening
- 91 2. TEE group: Transesophageal echocardiography for LAA thrombus
- 92 screening

- 93 • Study Type: Multicenter, randomized, open-label, parallel-group, non-
- 94 inferiority trial
- 95 • Target Sample Size: 1810 participants
- 96 • Start Date of Enrollment: August 2022

97

### 98 **1.3 Protocol Version and Date**

- 99 • Protocol Version: Version 3.1
- 100 • Date: July 10, 2022

101

## 102 **1.4 Funding and Support**

- 103 • This study is funded by the Biosense Webster Inc. USA.
- 104 • The sponsor had no role in the study design, data collection, analysis,
- 105 interpretation, manuscript writing, or publication decisions.
- 106 • This is an investigator-initiated and investigator-conducted study.

107

### 116 **Trial Governance Structure**

- 117 • Steering Committee: Oversees scientific conduct and governance
- 118 • Data Safety Monitoring Board (DSMB): An independent committee
- 119 responsible for ongoing safety surveillance, periodic review of accumulated
- 120 safety and efficacy data, and recommendations regarding study continuation,
- 121 modification, or termination. The DSMB operates under a predefined charter
- 122 and is independent from the sponsor and investigators.
- 123 • Clinical Endpoint Committee (CEC): An independent, blinded panel
- 124 responsible for reviewing and adjudicating all relevant safety and efficacy
- 125 endpoints to ensure objective outcome assessment.
- 126 • Data Management Team: Responsible for centralized data processing using an
- 127 electronic data capture system; each site retains medical records and
- 128 procedural data
- 129 • Contract Research Organization (CRO): Provides routine site monitoring and
- 130 ensures regulatory compliance
- 131 • Ethics Review: Conducted per Declaration of Helsinki, ISO 14155, and local
- 132 ethical requirements. All protocol amendments and SAE reports are submitted
- 133 to relevant IRBs/Ecs

## 2. Introduction

### 2.1 Background and Rationale

Atrial fibrillation (AF) is the most common sustained cardiac arrhythmia, characterized by rapid and irregular atrial electrical activity. This disrupts effective atrial contraction and hemodynamics, leading to blood stasis in the left atrial appendage (LAA) and significantly increasing the risk of thrombus formation. Studies have shown that the incidence of LAA thrombi in anticoagulated patients with AF ranges from 0.4% to 15.2%, depending on individual characteristics and comorbidities. The presence of LAA thrombus is considered an absolute contraindication to catheter ablation. Once detected, the procedure must be postponed until adequate anticoagulation therapy has resolved the thrombus.

Transesophageal echocardiography (TEE) has long been regarded as the gold standard for preprocedural LAA thrombus screening, with a reported sensitivity and specificity exceeding 90%. TEE enables high-resolution imaging by positioning an ultrasound probe in the esophagus, close to the heart. In a global survey of AF ablation centers, 73.2% reported routine use of TEE before ablation, regardless of patients' CHA2DS2-VASc scores. However, despite its diagnostic accuracy, TEE is semi-invasive and associated with discomfort and procedural risks such as gag reflex, sedation-related complications, and even esophageal injury. Additionally, when image quality is suboptimal, the sensitivity of TEE to exclude LAA thrombi is reduced. The proportion of equivocal TEE findings has been reported to be as high as 17.8%, leading to potential misdiagnosis and procedural delays.

Intracardiac echocardiography (ICE) is routinely used during AF ablation procedures for transseptal puncture guidance and complication monitoring. Emerging evidence suggests that ICE, when performed from appropriate positions such as the pulmonary artery or right ventricular outflow tract, may allow for reliable detection of LAA thrombi. Studies by Di Biase et al., involving over 7,000 patients undergoing uninterrupted anticoagulation and AF ablation, demonstrated the safety and feasibility of using ICE as an alternative to TEE for preprocedural thrombus screening. A recent retrospective study also showed that ICE provides comparable thrombus detection and complication rates, with added advantages such as lower post-procedural fever and improved hospital efficiency. However, these findings are derived from retrospective or non-randomized studies, limiting the strength of the evidence.

In the ICE-CHIP trial, ICE showed lower sensitivity for LAA thrombus detection compared to TEE, likely due to the limited imaging range as the catheter remained in the right atrium. With advancements in imaging technology and catheter positioning, ICE can now offer high-resolution visualization of the entire LAA, enabling its use as a potential replacement for TEE. While recent consensus documents from EHRA/HRS and China acknowledge the potential of ICE to replace TEE in LAA thrombus assessment, the recommendation remains weak due to the lack of randomized controlled evidence.

Therefore, we designed this prospective, multicenter, randomized controlled trial to systematically evaluate the diagnostic performance, safety, and clinical utility of ICE versus TEE in LAA thrombus screening before AF ablation. This study aims to fill the current evidence gap and provide high-level clinical data to support guideline recommendations and optimize procedural workflows.

In this study, **periprocedural embolic events**—including stroke, transient ischemic attack (TIA), and systemic embolism—were selected as the **primary endpoint**, rather than the thrombus detection rate. This decision was based primarily on **patient-centered clinical decision-making**. In real-world practice, the purpose of preprocedural screening is not merely to identify thrombi but to prevent actual thromboembolic complications during or after ablation. Hard endpoints such as stroke more directly reflect the clinical effectiveness of different strategies, whereas thrombus presence is only a surrogate marker. Thus, using embolic events as the primary endpoint enhances both the interpretability and real-world applicability of the findings, ultimately improving patient care.

## 2.2 Objectives

The primary objective of this study is to evaluate whether ICE is non-inferior to TEE in excluding LA or LAA thrombus prior to AF ablation. By accurately identifying patients without thrombus, the study aims to determine whether ICE can serve as a safe and effective alternative imaging modality, potentially reducing thrombus-related procedural complications and improving procedural workflow.

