### **Rationale for Non-Inferiority Margin**

The non-inferiority margin ( $\Delta = 0.8\%$ ) was selected based on clinical and statistical justifications. Although the anticipated difference between the ICE and TEE groups is only 0.1%, the margin reflects the maximum clinically acceptable increase in thromboembolic risk, as supported by prior literature and expert consensus. In the context of extremely low event rates (0.5% – 0.6%), using a wider margin allows for a feasible study sample size without compromising patient safety or trial integrity. Furthermore, demonstrating that the upper limit of the 95% confidence interval remains within the 0.8% margin ensures clinical comparability. This design strategy is consistent with FDA and EMA guidance for non-inferiority trials with binary safety endpoints.

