## 351 **3.5 Endpoints**

## Primary Endpoints

The primary endpoint centers on thromboembolic events occurring during the periprocedural period, which encompass:

- Stroke: Characterized as an abrupt onset of neurological dysfunction resulting from disrupted cerebral blood flow, causing tissue damage. Diagnosis is confirmed via MRI or CT imaging.
- Transient Ischemic Attack (TIA): A brief episode of neurological dysfunction due to temporary interruption of blood supply to a localized area of the brain. Symptoms typically resolve within 24 hours.
- Systemic Embolism: Sudden blockage of a blood vessel by an embolus, resulting in tissue ischemia or infarction in an organ other than the brain.

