## Secondary Endpoints

The prespecified secondary endpoints include:

- The detection rate of thrombus.
- Death related to the radiofrequency ablation procedure.
- Major bleeding complications: pericardial effusions and cardiac tamponade.
- Minor bleeding complications: vascular complications such as pseudoaneurysms, arterio-venous fistulas, and hematomas.
- Procedural characteristics: total procedure time, fluoroscopy time, and radiofrequency delivery time.
- Pre-procedural psychological state: Assessed using the Hospital Anxiety and Depression Scale (HADS), 14a self-assessment questionnaire measuring anxiety and depression levels in patients receiving medical care. Higher scores indicate more severe symptoms.
- Procedural pain degree: Measured using the Numeric Rating Scale (NRS), where patients rate their pain on a scale from 0 (no pain) to 10 (worst possible pain).
- Hospitalization cost: Expenses incurred during a patient's hospital stay, including charges for medical services, procedures, medications, accommodations, and other related expenses.
- Preprocedural waiting time: The period of time a patient waits before undergoing ablation.

These well-defined endpoints will help the researchers assess the effectiveness, safety, and patient experience of using ICE compared to TEE in patients undergoing AF ablation.

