#### **Secondary Endpoint Analysis**

- 508 • Continuous variables (e.g., procedure time, pain scores): Presented as mean  $\pm$   
509 SD or median (IQR); Compared using t-test or Wilcoxon rank-sum test  
510 (based on normality).
- 511 • Categorical variables (e.g., thrombus detection, bleeding): Expressed as counts  
512 and percentages and compared using chi-square or Fisher's exact test.
- 513 • Binary secondary endpoints were reported as relative risk (RR) with 95% CIs;  
514 continuous endpoints were expressed as mean difference (MD) with 95% CIs.
- 515 •

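### The primary objective claims non-inferior thrombus exclusion, but the only non-inferiority test is on periprocedural embolic events and cannot establish that claim

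*Protocol*

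**What the plan says.** Protocol section 2.2 gives the primary objective as to "evaluate whether ICE is non-inferior to TEE in excluding LA or LAA thrombus prior to AF ablation". Its second sentence speaks of accurately identifying patients without thrombus. Section 2.1 says the trial is designed to "systematically evaluate the diagnostic performance, safety, and clinical utility of ICE versus TEE in LAA thrombus screening before AF ablation".

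The endpoint and analysis sections ask a different question:

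- Section 2.1 states that embolic events "were selected as the primary endpoint, rather than the thrombus detection rate", and treats thrombus as a surrogate.
- Section 3.5, Primary Endpoints: "The primary endpoint centers on thromboembolic events occurring during the periprocedural period", namely stroke, TIA and systemic embolism.
- Section 5.4, Primary Endpoint Analysis: non-inferiority is concluded if the upper 95% limit of the risk difference in those events is below 0.8%.
- Section 3.5, Secondary Endpoints, lists "The detection rate of thrombus". Section 5.4 handles it under "Categorical variables (e.g., thrombus detection, bleeding): Expressed as counts" and percentages, with a chi-square or Fisher's exact test and no margin.

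On the margin, section 3.2 expects 0.5% with TEE and 0.6% with ICE. Its rationale calls 0.8% the largest clinically acceptable increase and adds that "using a wider margin allows for a feasible study sample size without compromising patient safety or trial integrity". It does not state what ICE event rate the margin tolerates.

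**The concern.** The objective is diagnostic and the test is on clinical outcome. A positive primary result would answer the objective as worded only if embolic events were a close proxy for missed thrombus. If they are not, a report that follows section 2.2 literally would claim more than the data can carry. This matters because section 2.1 says the trial is meant to supply evidence for guideline recommendations on replacing TEE.

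**Working it through.** **1. Can any planned analysis answer section 2.2 as worded?**

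- Section 3.4 describes ICE screening in one arm and TEE screening in the other. No patient is described as having both, and no common reference standard is named. Sensitivity, specificity and negative predictive value cannot be estimated.
- Detection rates by arm are compared, but without a non-inferiority margin. A detection rate also mixes prevalence, sensitivity and false positives.
- The arms differ in more than screening. In the ICE arm, ICE also supports geometry construction, transseptal puncture and effusion monitoring. In the TEE arm, puncture is guided by fluoroscopy. A difference in embolic events, or its absence, belongs to the whole strategy.

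So no planned analysis tests the stated objective.

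**2. What the margin tolerates (rates from section 3.2)**

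- Margin relative to the expected TEE rate: 0.8 / 0.5 = 1.6.
- ICE rate at the margin: 0.5% + 0.8% = 1.3%.
- That rate relative to TEE: 1.3 / 0.5 = 2.6.

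**3. How strongly the embolic endpoint reflects screening quality**

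Take the extreme case of an ICE probe that misses every thrombus, with all else equal between arms:

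excess risk = prevalence × TEE sensitivity × embolic risk per missed thrombus

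Inputs:

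- Prevalence 0.4% to 15.2% (section 2.1).
- TEE sensitivity 90% (section 2.1 says above 90%).
- TEE event rate 0.5% (section 3.2).
- 905 per arm (1810 randomized 1:1, section 2.3).
- Embolic risk per missed thrombus: **not in the protocol**. It is an assumption, varied here from 5% to 100%.

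Upper bound at 0.4% prevalence: 0.4% × 1 × 1 = 0.4 points, which is inside the 0.8-point margin even if every missed thrombus embolises.

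A true excess inside the margin is not the same as passing, because the rule uses the upper confidence limit. The pass probabilities below come from exact binomial enumeration of the Farrington–Manning test (z ≤ −1.96 against 0.8 points) at 905 per arm, TEE at 0.5%.

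| Prevalence | Embolic risk per missed thrombus (assumed) | Excess, points | Chance of passing |
|---|---|---|---|
| any | ICE equal to TEE | 0 | 53% |
| 0.4% | 5% | 0.4 × 0.9 × 0.05 = 0.018 | 50% |
| 0.4% | 20% | 0.4 × 0.9 × 0.20 = 0.072 | 43% |
| 0.4% | 100% | 0.4 × 0.9 × 1.00 = 0.36 | 15% |
| 2% | 20% | 2 × 0.9 × 0.20 = 0.36 | 15% |
| 5% | 20% | 5 × 0.9 × 0.20 = 0.90 | 1% |
| 15.2% | 5% | 15.2 × 0.9 × 0.05 = 0.684 | 3% |
| 15.2% | 10% | 15.2 × 0.9 × 0.10 = 1.368 | 0.1% |

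At a true excess of exactly 0.8 points the chance is 2%, so the test holds its nominal error at the margin.

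The 53% for equal rates is low because of the sample size, which is a separate matter. The section 3.2 formula reproduces (7.84 × 0.010939 / 0.000049 = 1750.24, against 1750.45 printed), but it gives a number per arm and the protocol uses it as the total. What counts here is the small gap between 53% and 43%.

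**The case against.** The strongest defence is that nothing is concealed. Section 2.1 argues openly for a patient-centred endpoint over a surrogate, the title concerns periprocedural complications, and the decision rule in section 5.4 is confined to thromboembolic events. The second sentence of section 2.2 also mentions a safe and effective alternative and thrombus-related complications. All of this stands: the endpoint is a reasonable choice and is not the fault. It is also the reason the first sentence of section 2.2 should match it.

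A reader might infer three stronger things, which the documents do not support:

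- *That a probe detecting nothing would pass.* This depends on prevalence and on an embolic risk that the protocol does not give. At the upper end of the prevalence range such a probe would nearly always fail. Comparing the true excess with the margin also misleads, since a true excess close to 0.8 points passes only about 2% of the time.
- *That the margin is 2.6 times the TEE rate.* The margin is 1.6 times that rate; 2.6 is the tolerated ICE rate over the TEE rate.
- *That the margin is shown to be unsafe.* The rationale appeals to prior literature and expert consensus that are not available here. Whether 1.3% against 0.5% is acceptable is a clinical judgement, and the assurance about patient safety is not a demonstrated error.

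Nor is detection by arm missing. It is already a secondary endpoint, reported with counts, percentages and a relative risk with 95% CI.

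**Conclusion.** The objective in section 2.2 and the promise of diagnostic performance in section 2.1 do not match the primary test. That conclusion needs no numerical assumption: it follows from the endpoint, the single modality per patient, the lack of a reference standard and the differing transseptal guidance. Meeting the margin would support a statement about periprocedural embolic events under two strategies, and nothing about equal thrombus exclusion.

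The weak link between the endpoint and screening quality is a supporting argument and is conditional. At 0.4% prevalence and an assumed 20% embolic risk, a probe missing every thrombus passes about 43% of the time, against 53% for one equal to TEE. This falls to 15% if every missed thrombus embolises, and to about 3% or less at 15.2% prevalence with an embolic risk of 5% or more. The calculation assumes a TEE event rate of 0.5%, TEE sensitivity of 90%, 905 per arm and no other difference between arms.

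**What to change.** - **Section 2.2:** restate the primary objective as non-inferiority of an ICE-guided to a TEE-guided screening strategy for periprocedural thromboembolic events (stroke, TIA, systemic embolism). Add that a positive result supports no claim of equivalent thrombus exclusion or diagnostic accuracy.
- **Section 2.1:** bring the reference to diagnostic performance into line with this.
- **Rationale for the margin (section 3.2):** state that 0.8 points is 1.6 times the expected TEE rate and tolerates an ICE rate of 1.3% against 0.5%, a ratio of 2.6.
- **Section 5.4:** report event counts by arm and the relative risk with 95% CI beside the primary risk difference. At present the relative risk is specified only for binary secondary endpoints.

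The cost is some rewording, one extra reported estimate and a narrower permitted claim. Endpoint, margin and sample size are unchanged by this point.

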## 2.3 Trial Design

This study is a multicenter, prospective, randomized, open-label, parallel-group, non-inferiority trial. A total of 1810 patients undergoing AF ablation were randomized 1:1 to receive either ICE-guided or TEE-guided thrombus screening. Outcome assessors, including the Clinical Endpoint Committee (CEC), are blinded to group allocation.

[figure not shown]

Figure 1. Trial design

### 3. Methods: Participants, Sample size justification , Interventions, and Endpoints

#### 3.1 Study Setting

This multicenter study was conducted at 10 tertiary medical institutions across China, including Shanghai Chest Hospital, Ren Ji Hospital, and eight additional high-volume centers specializing in AF ablation (see Appendix for full list of participating sites). All centers possess substantial expertise in AF ablation and intracardiac imaging, thereby ensuring strict adherence to the study protocol and high procedural quality.

#### 3.2 Sample size justification

The sample size calculation is based on the hypothesis and study design. For this non-

inferiority trial, the following parameters were used:

Type I error ( $\alpha$ ) = 0.025, corresponding to a Z-value ( $Z_{\alpha}$ ) of 1.96

Type II error ( $\beta$ ) = 0.2, corresponding to a Z-value ( $Z_{\beta}$ ) of 0.84

Expected event rate in the ICE group ( $p_1$ ) = 0.6%

Expected event rate in the TEE group ( $p_2$ ) = 0.5%

Non-inferiority margin ( $\Delta$ ) = 0.8%

These values were plugged into the sample size calculation formula for non-inferiority studies:

$$n = (Z_{\alpha} + Z_{\beta})^2 \cdot (p_1(1 - p_1) + p_2(1 - p_2)) / (p_1 - p_2 - \Delta)^2$$

$$n = (1.96 + 0.84)^2 \cdot (0.006(1 - 0.006) + 0.005(1 - 0.005)) / (0.006 - 0.005 - 0.008)^2$$

$$n = 7.84 \cdot (0.006 \cdot 0.994 + 0.005 \cdot 0.995) / (-0.007)^2$$

$$n = 7.84 \cdot 0.010939 / 0.000049$$

$$n = 1750.45$$

Based on this calculation, a sample size of approximately 1750 patients is required to achieve 80% power at a 5% significance level, assuming a non-inferiority margin of 0.8%. The actual recruited sample size of 1810 patients is slightly higher than the calculated sample size, indicating that the study's statistical power might be slightly higher than the anticipated 80%.

If the expected dropout rate is 2%, the sample size should be adjusted accordingly. The adjusted sample size can be calculated using the following formula: Adjusted sample size = Original sample size / (1 - Dropout rate)

In this case, the original sample size is 1750 patients (875 in each group). Applying the dropout rate adjustment: Adjusted sample size =  $1750 / (1 - 0.02) = 1750 / 0.98 = 1786$  (rounded up).

Therefore, to maintain the desired statistical power and significance level while accounting for the expected 2% dropout rate, a total of 1786 patients (approximately 893 in each group) should be recruited.

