## **8.3 Planned Sample Size Adjustment**

The originally planned sample size of 1200 cases was increased to 1786 due to modification in the primary study endpoints during the trial. Detailed sample size calculation methods are outlined in Section 3.2.

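### The sample size formula gives 1750 patients per group, but the protocol takes 1750 as the total, so power at 1810 patients is about 52% (about 40% with Farrington-Manning), not 80% or more

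*Protocol*

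**What the plan says.** Section 3.2 sets a type I error of "0.025, corresponding to a Z-value" of 1.96, a type II error of "0.2, corresponding to a Z-value" of 0.84, expected event rates of 0.6% (ICE) and 0.5% (TEE), and a margin of 0.8%. It prints a formula with p1(1 − p1) + p2(1 − p2) in the numerator and obtains n = 1750.45.

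It reads that result as the whole trial: "a sample size of approximately 1750 patients is required to achieve 80% power at a 5% significance level", and again, "In this case, the original sample size is 1750 patients (875 in each group"). Dividing by 0.98 for 2% dropout gives 1786 in total, about 893 per group. It compares the 1810 patients recruited with 1750, "indicating that the study's statistical power might be slightly higher than the anticipated 80"%.

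The same figures appear elsewhere. Section 8.3 records that "The originally planned sample size of 1200 cases was increased to 1786" and refers to section 3.2 for the method. Section 1.2 gives "Target Sample Size: 1810 participants". Section 2.3 says the 1810 were randomized 1:1.

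For the primary endpoint, the Statistical Methods section concludes non-inferiority if the upper bound of the 95% confidence interval for the risk difference is below 0.8%, and it names a Farrington-Manning interval. Another bullet there says logistic regression will be used to estimate the risk difference and its interval.

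**The concern.** With n patients in each group, the variance of the difference between two observed proportions is [p1(1 − p1) + p2(1 − p2)]/n. Solving the power equation for n gives the number in each group. Under 1:1 allocation the total is twice that, and the printed formula has no such factor. Halving the result to 875 per group leaves the trial at half the size its own calculation requires.

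Three things depend on this. First, the stated 80% power is the basis on which ethics committees and the DSMB would judge the enlarged trial after the change of primary endpoint. Second, the margin rationale that follows section 3.2 defends 0.8% partly because it makes the sample size feasible, and that argument uses a size understated by half. Third, a reader who believes power exceeded 80% could take a failed result as evidence against ICE, when failure was about as likely as success, or likelier, under the planning assumptions.

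**Working it through.** **Inputs (section 3.2).** z for one-sided 0.025 = 1.96; z for 80% power = 0.84; p1 = 0.006; p2 = 0.005; margin = 0.008. Allocation is 1:1 (section 2.3), so 1810 patients is 905 per group.

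**Reproducing the protocol's figure.**
- Variance sum: 0.006 × 0.994 + 0.005 × 0.995 = 0.005964 + 0.004975 = 0.010939.
- Squared distance to the margin: (0.006 − 0.005 − 0.008)² = 0.000049.
- n = (1.96 + 0.84)² × 0.010939 / 0.000049 = 7.84 × 0.010939 / 0.000049 = 1750.24.

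The protocol prints 1750.45, a trivial slip. With unrounded z values the result is 1753. The figure reproduces, but as a per-group size.

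**Corrected total.** 2 × 1750 = 3500. With 2% dropout, 3500 / 0.98 = 3571.4, or 3572.

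**Putting n back into the protocol's formula.** Power = Φ(0.007 / √(0.010939/n) − 1.96), with n per group:

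| n per group | Origin | 0.007 / SE | Power |
|---|---|---|---|
| 875 | 1750 read as total | 1.980 | 50.8% |
| 887 | 1810 less 2% dropout | 1.993 | 51.3% |
| 893 | 1786 in total | 2.000 | 51.6% |
| 905 | 1810 in total | 2.013 | 52.1% |
| 1750 | 1750 read as per group | 2.800 | 79.9% |

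Only the per-group reading returns the design power.

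**Can any other reading make 1750 or 1810 a valid total for 80% power?** Totals from the same type of formula:
- one-sided 0.025 as stated, unrounded z: 3506
- one-sided 0.05: 2762
- no true difference (0.5% in both groups), one-sided 0.025: 2442
- true difference in favour of ICE (rates swapped), one-sided 0.025: 2120
- no true difference and one-sided 0.05: 1924

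All exceed 1810. The mention of a 5% significance level does not help: at one-sided 0.05, 905 per group gives 64%.

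**Power of the Farrington-Manning rule.** This method takes its standard error from the two rates fitted under the constraint that they differ by exactly 0.8 percentage points. At the planning rates the constrained rates are 1.1386% and 0.3386%. With 905 per group:
- constrained SE = √[(0.011386 × 0.988614 + 0.003386 × 0.996614)/905] = 0.00402
- unconstrained SE = √(0.010939/905) = 0.00348
- asymptotic power = Φ[(0.007 − 1.96 × 0.00402)/0.00348] = Φ(−0.25) = 40.0%

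Exact power, summing binomial probabilities over all event counts that meet the rule at 0.6% against 0.5%:

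| ICE / TEE | Exact power |
|---|---|
| 875 / 875 | 40.4% |
| 887 / 887 | 39.9% |
| 893 / 893 | 39.7% |
| 904 / 906 | 39.3% |
| 905 / 905 | 39.2% |
| 906 / 904 | 42.0% |
| 906 / 906 | 42.1% |
| 1750 / 1750 | 72.6% |

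A simulation of 400,000 trials at 905 per group gave 39.3%. If both true rates are 0.5%, exact power at 905 per group is 53.0%. By the asymptotic formula, 80% power needs about 2157 per group.

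**What this means in events.** At 905 per group the planning rates imply 905 × 0.006 = 5.4 events on ICE and 905 × 0.005 = 4.5 on TEE. An observed 6 against 5 has a Farrington-Manning upper limit of 0.95% and fails.

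**The case against.** No reply restores 80%. The protocol itself writes 875 in each group, so the reading as a total is explicit and not an artefact of text extraction. Four qualifications deserve weight.

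- **Precision of the Farrington-Manning figure.** With so few events, exact power moves in steps. Randomization is simple and the modified intention-to-treat population includes only patients who underwent ablation, so 905 / 905 is not guaranteed. The figure is better given as about 40%, range 39% to 42%. For the same reason 5 against 5 events is a poor illustration: its upper limit is 0.8001% at 905 per group and 0.7992% at 906.
- **Which analysis governs.** The Statistical Methods section names both logistic regression and a Farrington-Manning interval without ranking them. The 40% applies if Farrington-Manning governs. An unpooled Wald rule enumerated exactly at 905 per group gives about 53%. The 52% from the protocol's own formula does not depend on this.
- **Scope of the correction.** Section 8.3 records a change that was made, and 1810 in section 1.2 is an enrolment figure. Neither states a power, so the correction belongs in section 3.2.
- **Consequence.** The error leaves the margin and decision rule as they are and would not invalidate a non-inferiority conclusion. The protocol never says that failure to show non-inferiority means ICE is inferior.

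These points narrow the figures and the remedy. They do not touch the error.

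**Conclusion.** The concern holds. Section 3.2 uses a per-group result as a total. With 1810 patients, power is 52% by the protocol's own formula, about 28 percentage points below the stated level, and about 40% with Farrington-Manning, about 40 points below.

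These figures assume the protocol's planning rates, a one-sided 0.025 test against 0.8%, and about 905 analysed patients per group. A 2% loss changes them little (51.3% and 39.9%). The 52% needs nothing beyond the printed formula and inputs; the 40% also requires that the Farrington-Manning interval decides the primary endpoint. The harm is a materially false power statement and a high chance of an inconclusive trial. It does not raise the risk of a false non-inferiority claim.

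**What to change.** Correct section 3.2 as follows:

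1. State that the formula gives 1750 patients per group, that is 3500 in total, or about 3572 with 2% dropout.
2. State alongside this that 1750 per group gives only about 73% power with Farrington-Manning, so that 3500 does not become a second unsupported 80% claim.
3. State that 1810 patients (905 per group) give about 52% power by the printed formula and about 40% with Farrington-Manning.
4. Delete the sentence saying that power may be slightly higher than 80%, together with the statements that 1750 or 1786 patients in total deliver 80%.

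The change record in section 8.3 can stand, since it refers to section 3.2 for the method. It would be helpful, though not needed to correct the arithmetic, to say that an upper limit above 0.8% will be read as inconclusive.

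The cost is wording only. No added enrolment is asked for and the decision rule does not change, but the stated power becomes much less favourable.
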